### Secondary outcomes

➢ Skeletal muscle molecular characteristics will be assessed in skeletal muscle vastus lateralis biopsy tissues from participants included in the study who agree to undergo the biopsy procedure (only at the Norwegian site: T0, T3).
◦ Myogenic stem cell count◦ Autophagy◦ Capillary number per muscle fiber◦ Macrophage infiltration◦ Markers of skeletal muscle catabolism➢ Patient-reported outcome measures (T0, T1, T2, T3, T4)◦ Self-reported fatigue assessed by means of the validated European Organization for Research and Treatment of Cancer Fatigue questionnaire (EORTC QLQ-FA12).◦ Health-related quality of life (HRQoL) assessed by means of the validated Quality of Life Core Questionnaire (EORTC-QLQ-C30)◦ Nutritional status will be assessed by means of the validated Patient-Generated Subjective Global Assessment scale (PG-SGA).➢ Physical fitness/performance/activity
◦ Physical function determined by the short physical performance battery and a submaximal and maximal (ramp) cycle test to evaluate cardiorespiratory fitness and maximal isometric muscle strength evaluated in a standardized manner (T0, T1, T2, T3)◦ Objectively measured physical activity and sedentary behavior using the Fitbit activity monitor (T0, T1, T2, T3, T4)➢ Clinical outcomes will be recorded retrospectively from the patient’s medical records (T4)
◦ Hospitalization rates◦ Blood status➢ Vital signs and anthropometrics
◦ Body composition using bioimpedance analysis (T0, T1, T2, T3)◦ Body composition using dual x-ray absorptiometry (only at the Norwegian site: T0, T3)◦ Body composition will also be measured using computed tomography (CT) scans when performed as a routine measurement for the patients (T0, T4). Thus, no extra CT scans will be conducted for the purpose of this study to minimize exposure to radiation.➢ Explorative outcomes

Patient’s experience of the exercise program, protein supplement, and activity tracker through focus group or individual interviews will take place sometime following the exercise intervention for a voluntary subset of the included participants in the exercise group.

### Participant timeline {13}

Study outcomes will be measured at baseline (T0) and immediately (1–4 weeks) after the prehabilitation period (T1), after surgery prior to the rehabilitation period (T2), and after the 5–6-week postoperative rehabilitation period (T3). A follow-up assessment (T4) will take place 6 months following surgery. Patients with short time-to-surgery will only perform (T0) prior to surgery or will be included at (T2) for the rehabilitation period. Focus group or individual interviews will take place sometime following the exercise intervention. Hospitalization rates, prognostic- and blood markers will be assessed retrospectively at (T4) through the patients’ medical records. Baseline testing will begin immediately as participants are recruited and randomization will occur directly after the initial testing session (T0). Exercise training for the intervention group will start once participants have completed baseline testing. See Fig. 2 for an overview of the study design and measurement outcomes and time points.

**Fig. 2 Fig2:**
[figure not shown]
The modified SPIRIT study flow chart

### Sample size {14}

To achieve 80% power at an alpha level of 0.05 (two-tailed) from pre- to post-intervention based on a magnitude of change of 1 mm in skeletal muscle thickness [13], and a standard error of measurement of 0.8 mm [14], a total of 42 participants are required. According to previous findings [5], we anticipate that 25% of the participants may drop out of the study; therefore, a total of 52 participants will be required to confirm or refute our hypothesis.

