### Trial design {8}

This Prev-Ex is a multi-center, two-armed randomized controlled trial (RCT) with 1:1 allocation ratio, stratified for research site, and testing the superiority of the intervention. Patients diagnosed with resectable pancreatic, biliary tract, and liver cancer are randomized to an exercise program consisting of home-based low-load BFR-T during both a pre- and postoperative period consisting of a total of 6–10 weeks, or a control group. Besides the nutritional support offered as standard care for these patients, protein supplementation will be given to both groups to ensure adequate protein intake. See Fig. 1 for the modified SPIRIT study flow chart.

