## Statistical methods

### Statistical methods for primary and secondary outcomes {20a}

Data will be analyzed using the IBM SPSS (Statistical Package for the Social Sciences) 26 statistical package for Windows (SPSS, Chicago, IL, USA). For the quantitative analysis, descriptive statistics, ANOVA, and chi-squared tests will be used to describe and compare baseline characteristics. For longitudinal analysis, linear mixed modeling adjusted for baseline values (T0) of the outcome will be used to detect any significant differences between the two groups from pre- to post-intervention as well as at follow-up 6 months following surgery. Group-by-time interaction will be included as a fixed effect. Corresponding effect sizes will also be calculated. Chi-squared tests and corresponding odds ratios will be calculated for hospitalization rates. All tests will be 2-tailed and statistical significance set at *p* ≤ 0.05.

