Due to the COVID-19 pandemic, the study start was delayed for almost 1 year. The initial plan was to include a more homogenous group: patients diagnosed with pancreatic or biliary tract cancer undergoing a pancreaticoduodenectomy; however, there were major challenges with the inclusion rate resulting in the study taking longer and risking a loss of statistical power. Amendments were made to the original plan to expand the inclusion criteria to patients undergoing either pancreaticoduodenectomy or laparoscopic surgery and to also patients with malignancies in the liver amendable for surgical resection. These changes were approved by the Swedish Ethical Review Authority and the Norwegian Regional committees for medical and health research ethics. We are aware that this will result in a heterogeneous group of patients. There is considerably less risk of complications for patients undergoing laparoscopic surgery compared to a pancreaticoduodenectomy; however, these potential differences will be adjusted for in the statistical analysis. Moreover, time to surgery and post-surgery recovery are similar across the diagnoses. In this study, we decided to include any patient who is diagnosed with resectable pancreatic, biliary tract, or liver cancer regardless of time-to-surgery which means that some patients will only have time to perform (T0) before surgery, while some will perform both (T0) and (T1). In some cases, time-to-surgery is only a few days which means that inclusion is not possible at (T0) but will instead take place at (T2). The reason for including patients at (T2) is that time-to-surgery is significantly shorter at the Norwegian site; consequently, amendments to the original plan had to be made to accommodate for the reduced time-to-surgery. We will perform a subgroup analysis to evaluate the rehabilitation effect (T2 to T3). Other amendments to the original plan include the addition of digitally supervised exercise and an exercise diary to be able to monitor exercise adherence more efficiently.

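### The 80% power claim rests on the ultrasound's measurement error and leaves almost no room for real differences between patients in how much muscle they gain or lose

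*Protocol article*

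**What the plan says.** The Sample size section (item 14) of the protocol article asks for 80% power at "an alpha level of 0.05 (two-tailed) from pre- to post-intervention". The target is 1 mm in skeletal muscle thickness, with "a standard error of measurement of 0.8 mm [14], a total of 42 participants are required". The 0.8 mm is the only variability figure given. No between-patient SD of thickness, or of its change, appears anywhere in the article. After a dropout allowance the section arrives at 52 participants, a number it presents as enough to settle the hypothesis either way.

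Trial design (item 8) describes a "two-armed randomized controlled trial (RCT) with 1:1 allocation ratio, stratified for research site, and testing the superiority of the intervention". Statistical methods (item 20a) plans a linear mixed model adjusted for the baseline value, to detect "any significant differences between the two groups from pre- to post-intervention".

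On the patients, the Discussion says of the widened eligibility: "We are aware that this will result in a heterogeneous group of patients". It names different operations with different complication risks, and it expects individual adaptation of the exercise. Prehabilitation lasts 1 to 4 weeks (item 11a), but some patients have very little of it or enter only after surgery (item 20b and Discussion).

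**The concern.** The SEM answers one question: if the same person is scanned again with no change in the muscle, how far apart are the readings? The trial asks another: do two groups of patients differ in how much their muscle changes? The SD for that question has two parts. One is the error of the two scans that form each change. The other is the real spread of change between patients in the same arm. The stated input covers only the first part.

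If the second part is not close to zero, the trial has less power than stated. The conclusion is then at stake. A non-significant result in a trial said to have 80% power invites the reading that the training does not preserve muscle, when the data may only be too few to tell.

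**Working it through.** **Inputs from the article.** Two-sided α = 0.05, power 80%, difference δ = 1 mm, SEM = 0.8 mm, two arms, 1:1, total 42 (21 per arm).

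**Reproducing 42.** The two-sample formula is n per arm = 2(1.960 + 0.842)² × SD² / δ² = 15.70 × SD² for δ = 1 mm.

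- SD = 0.8 mm: 15.70 × 0.64 = 10.05, rounded up to 11 per arm, total 22 (t-test: 11.1 per arm, total 24). This is not 42.
- SD of a difference of two scans with measurement error only: √(0.8² + 0.8²) = √1.28 = 1.131 mm. Then 15.70 × 1.28 = 20.09, rounded up to 21 per arm, **total 42**. This matches. The t-test needs 21.1 per arm, and 21 per arm gives 79.8% power.
- Other variants with SD 1.131 mm do not match: one-sided gives 32, 90% power gives 54, and a one-sample test of change gives about 13.

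**Room left for real variation.** The largest SD of change that keeps 80% power at 21 per arm is √(21 / 15.70) = 1.157 mm (normal approximation). The SD left for true change is √(1.157² − 1.28) = √0.058 ≈ 0.24 mm. By t-test the limit is 1.129 mm, just below 1.131 mm, so nothing is left.

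**Power when patients differ.** Let τ be the between-patient SD of true change. The article gives no value, so τ is an assumption, shown over a range. The SD of change is √(1.28 + τ²). Power is for a 1 mm between-group difference with 42 evaluable, without baseline adjustment. The detectable difference is SD / 1.129.

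| Assumed τ (mm) | SD of change (mm) | Power, t-test | Power, normal approx. | Difference detectable at 80% power, t-test (mm) |
|---|---|---|---|---|
| 0 | 1.13 | 80% | 82% | 1.00 |
| 0.5 | 1.24 | 72% | 75% | 1.10 |
| 1.0 | 1.51 | 55% | 57% | 1.34 |
| 1.5 | 1.88 | 39% | 41% | 1.66 |

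**How much an adjusted model would have to recover.** To bring the SD back to 1.131 mm, the share of variance removed would have to be 1 − 1.28 / (1.28 + τ²): 16%, 44% and 64% for τ = 0.5, 1.0 and 1.5 mm.

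**The case against.** - **The √2 step is inferred.** The article does not state it. Under the normal approximation any SD from about 1.129 to 1.157 mm rounds up to 21 per arm, and a t-test rounded up gives 44 in total. This stands: measurement error alone is the best explanation of 42, not a proven one. The cited source cannot be checked either, and 0.8 mm might be a mislabelled SD. But 0.8 mm as an SD of change would give 22 to 24 patients, so relabelling alone would not rescue the calculation.
- **A reader might infer that the SEM was entered unchanged as the SD of change.** The arithmetic rules this out, because 42 patients would then have about 98% power. What is missing is the between-patient part.
- **A reader might infer that the 1 mm is a within-group change set against a between-group test.** The wording is loose, but item 20a uses the same pre-to-post phrase for the between-group contrast, and 42 follows when 1 mm is taken as a two-sample difference. Only a clearer label is needed.
- **Baseline adjustment and repeated measures may recover precision.** This is true in principle. The Sample size section does not invoke them and gives no correlation, so they do not support the 42. The fix allows for them.
- **The loss depends on assumed values.** It does. At τ = 0.5 mm it is only about 7 percentage points. The direction does not depend on the choice: any appreciable spread in true change lowers power unless adjustment makes up for it.

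**Conclusion.** The concern holds. The variability input is the wrong quantity for the planned comparison, and the stated 80% is consistent only with almost no real variation in change between patients. The article's own account of its patients and of their exposure to training makes that implausible. The power is therefore unsupported and probably too high: about 72%, 55% or 39% at assumed true-change SDs of 0.5, 1.0 or 1.5 mm with 42 evaluable, before any gain from adjustment.

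The documents do not support the stronger statement that the trial cannot detect 1 mm. The true-change SD is unknown, and the low end of the range costs little. Nor does the defect bias the effect estimate or raise the type I error. It limits what a null result can mean. The step from 42 to 52 for dropout is a separate matter and adds nothing to the figures here.

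**What to change.** 1. Replace the 0.8 mm SEM by a between-patient SD of change, or by the residual SD of the baseline-adjusted model. Take it from published data, or from trial patients with both T0 and T3, pooled without using allocation. Patients who enter at T2 have no T0 and cannot contribute.
2. Correct the pooled estimate for the group difference it contains. With 1:1 allocation a true difference δ adds δ²/4 to the pooled variance. For δ = 1 mm and SD 1.131 mm this gives √(1.28 + 0.25) = 1.24 mm, the same as the τ = 0.5 mm row, so an uncorrected estimate could show a shortfall that does not exist. Subtract δ²/4, or show the result with and without the correction.
3. Restate the power for 1 mm, labelled as a between-group difference, or the minimum detectable difference, at the planned 52. State the number expected to be evaluable.
4. Say in the plan that a non-significant result will be read from the confidence interval and not as refuting the hypothesis.

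The cost is a short arm-blind variance calculation or a literature value, and a few sentences. The stated power will look less favourable. No extra patients are needed.

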### Recruitment {15}

Fifty-two patients with pancreatic, biliary tract, and liver cancer (26 in each group) will be recruited from two sites: Karolinska University Hospital in Stockholm, and Oslo University Hospital in Oslo, Norway, based on the inclusion and exclusion criteria. Due to the pandemic, the start of the inclusion of the first participant was delayed. Recruitment of the first participant was in May 2022 at the Swedish site and in February 2023 at the Norwegian site and is ongoing. The expected time of the final recruitment of participants from both sites is the end of 2024, and with that, the first phase (T0 to T3) of the project will be completed.

After a patient expresses interest, a member of the medical staff will provide detailed trial information and screen for eligibility as per the inclusion and exclusion criteria. Once the participants wish to volunteer for the study and after a reasonable time for reflection, the participants then sign the written informed consent form prior to randomization and intervention.

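### Enrolling 52 patients does not preserve the required 42 after 25% dropout: it leaves 39, and 56 would be needed

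*Protocol article*

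**What the plan says.** The section Sample size {14} of the protocol article sets out the calculation in two sentences. The target is stated as "To achieve 80% power" with a two-sided alpha of 0.05, "based on a magnitude of change of 1 mm in skeletal muscle thickness" and "a standard error of measurement of 0.8 mm". From these it concludes that "a total of 42 participants are required". The dropout allowance follows: "we anticipate that 25% of the participants may drop out of the study; therefore, a total of 52 participants will be required".

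Recruitment {15} carries the result forward as the operating target: "Fifty-two patients with pancreatic, biliary tract, and liver cancer (26 in each group) will be recruited from two sites". The article gives no other dropout rate, required number or larger target, and it does not write out the formula that leads from 42 to 52.

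**The concern.** A dropout allowance is meant to leave the required number of patients once the expected losses have occurred. The 25% is expressed as a share of the participants in the study, so it applies to those enrolled. Taking 25% from 52 does not leave 42. The three figures (42 required, 25% lost, 52 enrolled) therefore cannot all hold.

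The enrolment target decides when recruitment stops, and the power statement is what readers will use to interpret a null result. The Discussion already reports recruitment difficulties that put power at risk, so there is little slack to absorb an optimistic target.

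**Working it through.** **Inputs from Sample size {14}:** two-sided alpha 0.05; power 80%; difference 1 mm; standard error of measurement 0.8 mm; 42 required; 25% dropout; 52 enrolled. **From Recruitment {15}:** 26 per group. **From Trial design {8}:** 1:1 allocation.

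**Step 1: reproduce the 42.** The article gives no standard deviation (SD) of change. Two readings of the 0.8 mm were tried in the two-group formula n per arm = 2 × (1.960 + 0.842)² × SD² / difference².

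- SD = 0.8 mm gives 10.05, rounded up to 11 per arm, or 22 in total. This does not match.
- SD = 0.8 × √2 = 1.13 mm gives 20.1, rounded up to 21 per arm, or 42 in total. This matches.

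The second reading is an assumption, adopted because it returns the stated figure. The standardised effect is then 1 / 1.13 = 0.884.

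**Step 2: reproduce the 52.**

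- 42 × (1 + 0.25) = 52.5, which is 52 rounded down.
- 42 / (1 − 0.25) = 56.0, which does not match 52.

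The multiplication by 1.25 is inferred from the figures. Another route to 52.5 is 42 / 0.80, but that would imply 20% dropout, not the 25% stated.

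**Step 3: what 52 delivers.**

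- Completers at 25% dropout: 52 × 0.75 = 39, a shortfall of 42 − 39 = 3.
- Largest dropout that still leaves 42: 1 − 42/52 = 19.2%, or 10 of 52.
- Enrolment that leaves 42 at 25% dropout: 56 (28 per group), which is 4 more than planned.

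None of Step 3 depends on an SD.

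**Step 4: effect on power** (two-sample t-test, two-sided 0.05, 1 mm difference).

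| Basis for the effect size | 42 completers (21/21) | 39 completers (20/19) |
|---|---|---|
| SD 1.13 mm, d = 0.884 (reproduces 42) | 79.8% | 76.6% |
| d = 0.886, solved so that 42 gives exactly 80% | 80.0% | 76.8% |
| SD 1.0 mm (illustrative) | 88.5% | 86.0% |
| SD 1.5 mm (illustrative) | 55.9% | 52.7% |

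The first two rows take the plan's 80% at 42 as given, and both come to about 77% at 39. The last two rows show that the loss stays at roughly 3 percentage points if the SD differs, although the absolute power changes a great deal.

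**The case against.** The arithmetic itself is not open to dispute. The arguments on the other side concern its weight and how it is expressed.

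- **The effect is small.** Three completers and about 3 power points change no test, estimand or allocation. This is true, and it limits the consequence. It does not make the stated figure right.
- **The 77% rests on an SD the article does not give.** As a statement about the trial's true power this is fair: a standard error of measurement describes measurement error, not how much patients differ in their change, and the SD range in the table matters. But the 77% is conditional on the plan's own claim of 80% at 42. Whatever effect size makes that claim true gives about 77% at 39. The basis of the 42 is a separate question, and settling it would not repair the dropout step.
- **The mixed model uses partial data.** The section on missing data {20c} says that all available visits enter the model, so a patient who leaves after T1 or T2 still contributes something. The sample size section does not use this argument to justify a smaller allowance; its allowance is there to replace patients who are lost. A patient with no measurement after baseline adds nothing on change, and dropouts miss T3, the visit that closes the intervention period.
- **The number with a T0-to-T3 change does not depend on dropout alone.** Some patients may enter first at T2 and have no T0 value. This stands as a point of wording: 39 is a count of completers, and "evaluable" would claim more than the figures show.

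**Conclusion.** The concern holds. On the plan's own figures, 52 enrolled with 25% dropout leaves 39 completers against 42 required, and the number that preserves 42 is 56. The shortfall of 3 needs no outside assumption. The associated loss of power is about 3 percentage points, from 80% to about 77%, provided the plan's claim of 80% at 42 is accepted. That the error came from multiplying by 1.25 is an inference, but the contradiction stands whichever formula was used. The practical effect is modest. The figure should still be corrected because it is the headline sample size and the recruitment target, and the correction costs very little.

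**What to change.** Correct the dropout sentence in Sample size {14} in one of two ways.

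1. **Keep 52 and restate what it delivers (preferred).** Suggested text: *With 25% dropout, 52 randomised participants leave 39 completers and about 77% power under the assumptions that give 80% with 42; 80% power holds only if dropout is at most 19%.* The cost is one sentence and a slightly less favourable power statement. No further patients are needed, and Recruitment {15} can stay as it is.
2. **Keep 80% power at 25% dropout.** State 56 participants (28 per group) in Sample size {14} and Recruitment {15}. The cost is 4 more patients and an amendment to the target. The article describes recruitment as still under way, so this was open to the sponsor at that version.

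Under either option, show the formula, 42 / (1 − 0.25), use the word completers, and align any other document that repeats the sample size statement.

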### Recruitment {15}

Fifty-two patients with pancreatic, biliary tract, and liver cancer (26 in each group) will be recruited from two sites: Karolinska University Hospital in Stockholm, and Oslo University Hospital in Oslo, Norway, based on the inclusion and exclusion criteria. Due to the pandemic, the start of the inclusion of the first participant was delayed. Recruitment of the first participant was in May 2022 at the Swedish site and in February 2023 at the Norwegian site and is ongoing. The expected time of the final recruitment of participants from both sites is the end of 2024, and with that, the first phase (T0 to T3) of the project will be completed.

After a patient expresses interest, a member of the medical staff will provide detailed trial information and screen for eligibility as per the inclusion and exclusion criteria. Once the participants wish to volunteer for the study and after a reasonable time for reflection, the participants then sign the written informed consent form prior to randomization and intervention.

